#### Historical comparators

We felt it was unethical to have a control group of patients with *DPYD* variants who undergo standard FP dose administration due to the well described increased risk of toxicity within this population [9, 10]. Therefore, comparator populations for this project will include:Current standard of care, as assessed by a retrospective review of 500 consecutive cases in NSW [31].Contemporaneous cases without these *DPYD* variants treated with standard doses,*DPYD* variant carriers in this study that do not receive PGx-guided dose-adjustment, and.Patients treated in European cohorts whereby *DPYD* variant carriers were treated with a 25% or 50% FP dose reduction.

Background ≥ G3 toxicity in an ungenotyped population is approximately 17.4%, and in *DPYD* variant carriers without FP dose adjustment is reported to be 39–61% [8, 31]. Sub-analyses for each *DPYD* variant will be included.

### Statistical considerations

#### Statistical hypotheses

We hypothesise that FP-induced severe toxicity (≥ G3) will decrease from 60% in the variant carriers receiving full dose chemotherapy to 35% in variant carriers receiving PGx-guided chemotherapy.

#### Sample size determination

This project intends to capture and test most feasibly large cohort of patients based on average clinical volume and anticipated number of patients that are eligible for testing across all study sites. Approximately 17000 patients are treated with FP per annum, resulting in > 30,000 potentially eligible patients across just 2 years of recruitment. As such, 5000 subjects in this study would require a recruitment capacity of < 15%. Our participating sites provide care for > 30% of Australians with cancer.

Based on expected frequency of *DPYD* variant alleles (~ 4% as a conservative estimate), testing *N* = 5000 patients will result in ~ 200 patients with actionable genotypes. Toxicity in these patients will be compared to historical datasets (Table 4). Assuming toxicity decreases to 35% in those receiving PGx- guided dosing, *N* = 70/arm will provide 80% power to detect a significant improvement in FP-related toxicity at the 5% level.

**Table 4 Tab4:** Populations for analysis

**Analysis Population**	**Description**
Testing Set	All patients who are eligible for recruitment and undergo* DPYD* genotyping
*DPYD *Set	Patients in this study who are found to carry a *DPYD *variant. Comparator groups include: 1) retrospective review of FP toxicity in *n*=500 patients who were treated without genotyping 2) contemporaneous cases without *DPYD *variants treated with standard doses 3) contemporaneous cases of *DPYD *variant carriers who do not receive dose-adjustment, and 4) *DPYD* variant carriers in European cohorts who were treated with dose reduction

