### Statistical analyses

Descriptive statistics on continuous data will include means, medians, standard, deviations, and ranges, while categorical data will be summarized using frequency, counts and percentages. Graphical summaries of the data may also be presented.

The 95% confidence intervals for the proportion of tests returned within 7 days of intended chemotherapy dosing and the proportion of PGx guided dosing adjustments implemented will be estimated using the Clopper-Pearson method. PGx-guided dosing will be deemed feasible to implement if both 95% confidence intervals are completely above 80%.

The proportion of DPYD positive patients experiencing ≥ G3 toxicities in the current sample will be compared to the historical controls using a Fisher’s exact test. Logistic regression will also be used to compare the rate of ≥ G3 toxicities between the two groups. The intervention effect will therefore be summarised using the odds ratio and 95% CI from this model.

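### The 80% power is calculated for 70 versus 70 carriers, but the plan identifies no full-dose carrier control group of a size that supports it

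*Protocol article*

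**What the plan says.** Under Statistical hypotheses, severe toxicity "will decrease from 60% in the variant carriers receiving full dose chemotherapy to 35% in variant carriers receiving PGx-guided chemotherapy". Under Sample size determination, the planning carrier frequency is "4% as a conservative estimate", so that testing 5000 patients "will result in ~ 200 patients with actionable genotypes", and "70/arm will provide 80% power to detect a significant improvement in FP-related toxicity at the 5% level".

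Historical comparators and Table 4 list four comparators:

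- a "retrospective review of 500 consecutive cases in NSW", which Table 4 describes as treated without genotyping;
- contemporaneous patients without the variants, on standard doses;
- study "variant carriers who do not receive dose-adjustment";
- European carriers who were treated with a dose reduction.

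Under Statistical analyses, carriers in the current sample are compared with historical controls by Fisher's exact test, without saying which comparator that is. The same section sets the feasibility rule on test turnaround and on the proportion of guided adjustments implemented: "PGx-guided dosing will be deemed feasible to implement if both 95% confidence intervals are completely above 80" per cent, with Clopper-Pearson limits.

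**The concern.** A per-arm figure implies two equal groups. The hypothesis fixes the control group as carriers on full dose, so the stated power presumes 70 of them. The article gives no count of full-dose carriers for any comparator, and the two comparators that could contain them look small at the plan's own prevalence. One of the two also shrinks as the feasibility goal is met: the more carriers are adjusted, the fewer unadjusted carriers remain.

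This is the article's only power statement, and it concerns a primary endpoint. If it does not describe the comparison that will be made, a non-significant result would be hard to interpret. Leaving the control group open would also allow it to be chosen after the data are seen.

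**Working it through.** **Inputs.** Toxicity 60% vs 35% (Statistical hypotheses). 5% level, 80% power, 70 per arm, about 4% prevalence, about 200 carriers in 5000 (Sample size determination). Review of 500 cases (Historical comparators). Clopper-Pearson lower limit above 80% (Statistical analyses). Sidedness is not stated; two-sided is assumed because it reproduces the figure.

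**1. The plan's own figure.** With p1 = 0.60, p2 = 0.35 and mean 0.475:

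n = [1.960·√(2·0.475·0.525) + 0.842·√(0.60·0.40 + 0.35·0.65)]² / 0.25² = 61.4 per arm.

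With continuity correction, (n/4)·[1 + √(1 + 4/(n·0.25))]² = 69.2, which rounds up to 70. Exact two-sided Fisher power at 70 vs 70 is 80.9%. The stated figure reproduces.

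**2. Which comparators can be the 60% arm.** Patients without variants are not carriers. The European carriers had reduced doses. That leaves the review and the unadjusted study carriers.

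**3. How many full-dose carriers each could supply.**

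- Review: 500 × 4% = 20, if its carriers can be identified; otherwise none.
- Unadjusted study carriers: of 200, 171 adjusted gives a Clopper-Pearson lower limit of 79.8% (fails) and 172 gives 80.4% (passes). So at most 200 − 172 = 28 are unadjusted if the feasibility rule is met.

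**4. Exact two-sided Fisher power at 60% vs 35%.**

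| Full-dose controls | Guided carriers | Power |
|---|---|---|
| 70 (as stated) | 70 | 80.9% |
| 20 (review only) | 200 | 53.6% |
| 28 (unadjusted study carriers, ceiling) | 172 | 66.9% |
| 10 (unadjusted study carriers, high adherence) | 190 | 33.8% |
| 48 (both pooled, 20 + 28) | 172 | 86.5% |

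**5. How many controls would suffice.** With 200 guided carriers, 38 controls give 80.8%. With 172, 39 give 80.4%. So about 38 to 40 are enough; 70 are needed only at 1:1.

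**6. Where the unadjusted carriers are counted.** Read literally, the Fisher test takes all carriers in the current sample. If 28 of the 200 are unadjusted and stay on that side, the expected rate is (172 × 0.35 + 28 × 0.60)/200 = 38.5%, and power against 20 review carriers is about 40%.

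**The case against.** A reader might infer that the design cannot reach 80% power, or that it is 42 to 50 controls short of a required 70. The documents do not support that, for four reasons.

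- The 70 holds only at equal allocation. Against the expected number of treated carriers, the benchmark is about 38 to 40.
- 20 and 28 are two separate sources, not the ends of a range. Together they could reach 48, and 48 vs 172 exceeds 80%. The health economic section does plan to draw its no-genotyping comparator from historical cohorts as well as from unadjusted study carriers.
- The comparator list is worded as inclusive. The abstract mentions historical cohorts of carriers not genotyped before exposure, and the health economic section mentions a linked dataset from historical cohorts. Neither has a stated size, and a fuller protocol may give one.
- The 4% is called conservative, and the Background gives about 8% for European-Caucasians. At 8% throughout, the review would hold 40 carriers and the study 400: 40 vs 400 gives 84.9%.

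All four stand against a flat claim of failure. They do not rescue the statement as printed. No section plans pooling for the Fisher test, and pooling reaches 48 only if the review's carriers are identified and the feasibility rule is just met. The 8% case also needs identified carriers in the review, and the article itself plans on 4%. An article may leave detail to a fuller document, but this one prints a specific power for a layout that its own comparator list does not provide.

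The 60% control rate lies near the top of the article's reported 39–61%. That is a separate matter: at 50%, even 70 vs 70 has only 36.8% power, so it is no evidence of a shortage of controls.

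**Conclusion.** The calculation is correct, but the layout behind it is not one that the article provides. At the planning prevalence, neither listed source of full-dose carriers reaches 80% power alone: about 54% for the review and at most about 67% for unadjusted study carriers. The historical comparison that the Fisher test names falls in the first case unless another cohort is meant. Pooling would give about 86% but is not planned.

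These figures assume 60% vs 35%, a two-sided 5% test, 200 study carriers and, for the 28, a feasibility rule that is just met. Supply could be lower (review carriers not identifiable, or high adherence) or higher (8% prevalence, or a further historical cohort). The supported conclusion is that the stated power has no identified control group behind it. Whether 80% is attainable is left open.

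**What to change.** Under Sample size determination, replace the per-arm figure with the actual unequal layout. Name the full-dose carrier control group for the primary Fisher test, how its carriers are identified (in particular, whether the 500-case review will be genotyped), and its expected number of carriers. Restate power for that layout. If only the listed sources are available and they are not pooled, give the lower figure: about 54% with 20 controls, or about 67% with 28. If the sources are to be pooled, say so in advance.

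Under Statistical analyses, replace the general reference to historical controls with the named group, and state whether unadjusted study carriers count as controls or remain in the current sample.

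The cost is a text change with no extra enrolment. The stated power may become less favourable, and genotyping the review, if chosen, would be additional work.

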### Statistical analyses

Descriptive statistics on continuous data will include means, medians, standard, deviations, and ranges, while categorical data will be summarized using frequency, counts and percentages. Graphical summaries of the data may also be presented.

The 95% confidence intervals for the proportion of tests returned within 7 days of intended chemotherapy dosing and the proportion of PGx guided dosing adjustments implemented will be estimated using the Clopper-Pearson method. PGx-guided dosing will be deemed feasible to implement if both 95% confidence intervals are completely above 80%.

The proportion of DPYD positive patients experiencing ≥ G3 toxicities in the current sample will be compared to the historical controls using a Fisher’s exact test. Logistic regression will also be used to compare the rate of ≥ G3 toxicities between the two groups. The intervention effect will therefore be summarised using the odds ratio and 95% CI from this model.

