## Methods/design

This is a single arm, non-randomised, multicentre prospective study. In recognition of the strong international data that show benefit for PGx-guided dosing, it is considered unethical for us to conduct a randomised controlled trial to directly compare the implementation and non- implementation of PGx-guided dosing. It is a collaborative, investigator-led initiative supported by a trial committee comprising researchers from most states in Australia.

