### Study population

We aim to enrol 5000 patients from hospitals across multiple states in Australia and including metropolitan, regional and rural cancer services. Eligible participants are 18 years and older with solid organ malignancies intended to receive FP chemotherapies (either 5-FU or capecitabine) and/or irinotecan chemotherapy as part of either curative or palliative cancer management either as single agents or in combination. Patients must be able to provide informed consent and capable of providing a blood sample for genotyping. Exclusion criteria include those who have received prior treatment with FP chemotherapies, or who decline consent or blood collection. Patients who are pregnant or breastfeeding are also excluded, as are those already enrolled in other clinical trials that are likely to influence toxicity outcomes.

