### Intervention

*DPYD* genotyping will be prospectively conducted in all patients prior to commencement of FP chemotherapies. Genotyping pathology services will be pre-determined by participating sites. Clinically significant *DPYD* variants will include c.1905 + 1G > A (rs3918290), c.2846A > T (rs67376798), c.1679 T > G (rs55886062) and c.1236G > A (rs56038477) (Supp Fig. 1). Patients found to carry one or more clinically significant variants will undergo dose-adjustment of FP chemotherapy prior to first administration, in accordance with eviQ guidelines (Supp Tables 1 and 2) [23].

◦ Heterozygote carriers of a single specified *DPYD* variant should receive a 50% dose-reduction prior to first FP exposure◦ Following this administration, patients should be reassessed and FP dose further down-titrated or ceased in response to G3-4 toxicity, or up-titrated for those who experienced minor or no toxicities. Suggested increment for titration is ± 12.5% (of the 100% recommended dose), as suggested by EviQ.◦ Patients who carry two variants (either compound heterozygote or homozygote carriers) should be dosed on an individual basis and may need to avoid FP administration altogether.

Data will be collected on all patients and will include specific datapoints for *DPYD* variant carriers who undergo dose-reductions to explore adherence to guidelines versus alternative dose-adjustment decisions. Bio-banked specimens from patients who do not have a pre-specified *DPYD* variant but experience ≥ G3 toxicities will undergo further exploratory genotyping. A subset of samples from patients intended to receive irinotecan chemotherapy will be batched and genotyped for clinically significant *UGT1A1* variants (*6 (*UGT1A1* c.211G > A), *28 A(TA)6TAA > A(TA)7TAA promoter), *37 (A(TA)6TAA > A(TA)8TAA promoter). Any *UGT1A1* genotype-guided dose-adjustment will be at clinician discretion. *UGT1A1* genotyping is for assessment of feasibility only. Data monitoring will be intermittently conducted by the trial management committee.

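### The turnaround feasibility interval treats about 5000 tests as independent, although turnaround depends on the site and its genotyping service, so it is too narrow for a claim about national roll-out

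*Protocol article*

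**What the plan says.** The Statistical analyses section of the protocol article names two proportions. The first is introduced as "The 95% confidence intervals for the proportion of tests returned within 7 days of intended chemotherapy dosing"; the second is the share of guided dose adjustments that are put into practice. The intervals for both "will be estimated using the Clopper-Pearson method". A decision is tied to them: "PGx-guided dosing will be deemed feasible to implement if both 95% confidence intervals are completely above 80" per cent. The method and the rule are thus fixed in the article, not left open for a later plan.

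Methods/design describes a "single arm, non-randomised, multicentre prospective study". Study population states: "We aim to enrol 5000 patients from hospitals across multiple states in Australia and including metropolitan, regional and rural cancer services". Intervention adds: "Genotyping pathology services will be pre-determined by participating sites". The Discussion names the geographical spread of laboratories and health services as a particular obstacle to short turnaround in Australia. The Abstract says that the feasibility estimates are meant to support national roll-out.

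On denominators, all enrolled patients are genotyped, which gives about 5000 tests. Sample size determination expects that 5000 "patients will result in ~ 200 patients with actionable genotypes". The article gives no number of sites or laboratories, no ICC, and no allowance for clustering in either interval.

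**The concern.** Clopper-Pearson is exact for independent observations with a common success probability. Whether a result comes back in time is settled largely by the laboratory, its batching and transport, and these are set at site level. Patients at one site, or served by one laboratory, will tend to share good or poor turnaround. With a hundred or more tests per cluster, even a small ICC inflates the variance of the pooled proportion considerably.

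The interval also serves as a decision rule. If it is too narrow, a pooled result only just above 80% could be declared feasible when the data cannot separate it from 80% for services outside the study.

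**Working it through.** **Inputs from the article.** 95% two-sided Clopper-Pearson intervals; threshold 80%; about 5000 tests; about 200 carriers. The article states no power or error rate for the feasibility rule, so there is no figure of its own to reproduce.

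**Assumed inputs.** K equal clusters (sites or laboratories) and ICC ρ. Neither is in the documents, so a range is shown.

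**Step 1: the rule under independence.** The smallest count whose lower Clopper-Pearson limit exceeds 80% is 4056/5000 (81.1%). At a true 80%, P(X ≥ 4056) = 2.4%. For 200 carriers the smallest count is 172/200 (86%), and at a true 80% the pass probability is 1.8%.

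**Step 2: design effect.** DE = 1 + (m − 1)ρ, with m = 5000/K. For K = 30 and ρ = 0.05, m = 166.7 and DE = 1 + 165.7 × 0.05 = 9.28. The effective sample size is 5000/9.28 = 539. At an observed 82%, the half-width under independence is 1.96 × √(0.82 × 0.18/5000) = 1.06 points; with clustering it is 1.06 × √9.28 = 3.2 points. At a true 80%, ρ = 0.05 means a between-site standard deviation of √(0.05 × 0.16) = 8.9 points.

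**Step 3: chance of meeting the turnaround condition at a true 80%.** Beta-binomial simulation, equal clusters, cut-off 4056/5000:

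| Clusters | ICC 0.005 | 0.01 | 0.02 | 0.05 | 0.10 | 0.20 |
|---|---|---|---|---|---|---|
| 15 | 11% | 17% | 24% | 33% | 38% | 42% |
| 20 | 9% | 15% | 21% | 30% | 36% | 41% |
| 30 | 7% | 11% | 17% | 26% | 33% | 38% |
| 50 | 5% | 8% | 13% | 21% | 28% | 34% |

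A normal approximation agrees: for K = 30 and ρ = 0.05, z = (4055.5 − 4000)/√(5000 × 0.16 × 9.28) = 0.64, a tail of 26%.

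**Step 4: the carrier interval.** With 200 carriers, m = 200/K and DE is small: 1 + (6.67 − 1) × 0.05 = 1.28 for K = 30 and ρ = 0.05. The pass rate at a true 80% is 1.8% to 4.1% for 20 to 50 clusters with ICC up to 0.05. It rises when clusters are few and the ICC is large: 6.3% for 20 clusters and 18% for 5 clusters, both at ICC 0.10.

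**Step 5: the two-part rule.** If both true proportions are 80% and the two conditions are treated as independent, the joint pass rate is the product of the two. For K = 30 and ρ = 0.05 this is 0.26 × 0.031 = 0.8%; for 20 or more clusters with ICC up to 0.05 it is at most 1.2%. If dose adjustment is truly about 95%, the second condition is met almost always (at least 99% over the table's range), so the rule's error is the figure in Step 3.

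**Step 6: away from the threshold.** At a true turnaround of 90%, the condition is met in about 99% to 100% of trials over the table's range.

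**The case against.** Three objections have force.

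First, both intervals must clear 80%. A reader might infer that the whole rule would be passed far too often as a general matter. The documents do not support that: with both proportions at 80% the joint pass rate is low (Step 5). The inflated rate is the rule's error only when turnaround sits at the boundary and adjustment is comfortably above it. That is still the relevant worst case for a rule requiring both conditions, but it is a condition and must be stated.

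Second, the target of inference. If only the participating sites matter, they are fixed strata; the variance of the pooled proportion is then no larger than binomial and Clopper-Pearson is, if anything, conservative. The concern holds only for inference to other sites. The stated aim of national roll-out points there. So does Sample size determination, which puts the participating sites' share at more than 30% of Australians with cancer and so leaves room for most to be treated elsewhere. However, the article never says that its sites are to be viewed as a sample of all sites.

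Third, it is tempting to read the article as saying that each site has its own laboratory, or that both intervals rest on 5000 tests. It says neither. Sites choose a service and may share one, and the Discussion speaks of local hubs. Sharing does not remove the problem: if the laboratory drives turnaround, fewer laboratories mean fewer and larger clusters.

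Feasibility is also a secondary objective, and no expected timely-return proportion is given to suggest a result near 80%. Both points limit the consequence without making the interval valid for the wider inference.

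**Conclusion.** The point holds for the turnaround interval when the inference is to national roll-out. Under 15 to 50 equal clusters and ICC 0.005 to 0.20, all assumed, the turnaround condition would be met at a true 80% in about 5% to 42% of trials instead of 2.4%. The width of that range reflects what the documents do not give, so no single value should be quoted as the trial's error rate. The practical consequence is confined to results near the threshold with good dose-adjustment uptake; at a true turnaround near 90% the conclusion is little affected. The carrier interval needs the same treatment for consistency, but its error changes little unless clusters are few or the ICC is large.

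**What to change.** Compute the feasibility limits, above all for turnaround, allowing for clustering by site or by laboratory where sites share one. A beta-binomial model, a site-level bootstrap or a GEE with small-sample correction would serve; with few clusters the small-sample behaviour of the chosen method should be checked. Apply the 80% rule to those limits, and state that the inference is to sites beyond those taking part. Site-level proportions shown beside the pooled result would let readers see whether a few large, fast sites carry it, since a wider interval alone does not change the weighting of the pooled estimate.

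The cost is a change of wording in the analysis plan and a little programming. Recruitment, data collection and sample size are unchanged. The downside is a wider interval, so feasibility becomes somewhat harder to declare: in the example with 30 clusters and ICC 0.05, the half-width at 82% goes from about 1.1 to 3.2 points, and an observed 82% would no longer clear the threshold.

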**Method:**

This investigator-led, single-arm study will determine large scale feasibility of prospective *DPYD* genotyping, confirming patient safety and cost-effectiveness within the Australian health care system. 5000 patients aged 18 years and older with solid organ cancers requiring FP chemotherapy will be consented and genotyped prior to commencing treatment, and early toxicity (within 60 days) post-FP exposure will be determined. Toxicity data for *DPYD* variant carriers who have dose adjustments will be compared to the wild-type cohort and historical cohorts of carriers who did not undergo genotyping prior to FP exposure, and prospective variant carriers who do not undergo dose-adjustment. Prevalence of the four standard *DPYD* gene variants will be confirmed in an Australian population. Additionally, health economic analysis, implementation research via semi-structured interviews of patients and clinicians, and feasibility of *UGT1A1* genotyping will be conducted.

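### The Fisher test of toxicity in carriers has no named control, and neither historical group in Table 4 is the full-dose carrier group behind the hypothesis and the 70 per arm

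*Protocol article*

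**What the plan says.** All references are to the protocol article.

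- **Statistical hypotheses:** severe toxicity "will decrease from 60% in the variant carriers receiving full dose chemotherapy to 35% in variant carriers receiving PGx-guided chemotherapy". Both sides of the contrast are variant carriers.
- **Sample size determination:** about 4% of 5000, or roughly 200 patients, are expected to have an actionable genotype. Their toxicity is to be compared with historical datasets, with a pointer to Table 4. "Assuming toxicity decreases to 35% in those receiving PGx- guided dosing", a group size of "70/arm will provide 80% power to detect a significant improvement in FP-related toxicity at the 5% level".
- **Table 4** lists four comparators for the DPYD Set: (1) a review of 500 "patients who were treated without genotyping"; (2) contemporaneous non-carriers at standard dose; (3) contemporaneous carriers whose dose is not adjusted; (4) European carriers given a reduced dose. The Historical comparators section lists the same four.
- **Historical comparators** also gives two background rates: severe "toxicity in an ungenotyped population is approximately 17.4"%, and 39–61% in carriers without dose adjustment.
- **Statistical analyses:** the proportion of carriers with severe toxicity "in the current sample will be compared to the historical controls using a" Fisher's exact test, followed by a logistic regression of the two groups. Which dataset supplies the controls is not said.
- **Abstract, Method:** one comparator is "historical cohorts of carriers who did not undergo genotyping prior to FP exposure".

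**The concern.** The test, the pointer and the list do not fit together. The hypothesis and the sample size need a control group of carriers treated at full dose, with about 60% toxicity. A reader who follows the plan from the test to Table 4 finds two groups that predate the study. One is not selected on genotype. The other consists of carriers who have already had the kind of intervention under study. The group that would match appears in the abstract but not in the list of comparators or in Table 4.

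This is the only comparative test described for toxicity in carriers, which is primary endpoint (b) in Table 2. Depending on which group is taken as the control, the same trial data could read as benefit, no difference or harm. A control that is left open can also be settled once results are known.

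**Working it through.** **1. Reproduce the plan's own figure.** Inputs: p1 = 0.60, p2 = 0.35, 80% power and a 5% level, taken as two-sided because the plan does not say.

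With p̄ = 0.475, n = [1.96·√(2·0.475·0.525) + 0.842·√(0.60·0.40 + 0.35·0.65)]² / 0.25² = 61.4, so 62 per arm. With the continuity correction, n' = (n/4)·[1 + √(1 + 4/(n·0.25))]² = 69.2, so 70 per arm. By exact enumeration, Fisher's test with 70 v 70 has 81.0% power. The stated figure is therefore sound, and it rests on full-dose carriers at 60% as the control.

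**2. Compare each Table 4 group with that control.**

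| Group | Carriers? | Full dose? | Historical? |
|---|---|---|---|
| 1. Review of 500 | not selected as carriers | not genotype-adjusted | yes |
| 2. Non-carriers in the study | no | yes | no |
| 3. Unadjusted carriers in the study | yes | yes | no |
| 4. European carriers | yes | no | yes |

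No row is carriers, full dose and historical at once.

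**3. Group 1 as the control.** Assumption: the 500-case review has the 17.4% rate, so 0.174 × 500 = 87 events. Hypothesised success: 0.35 × 200 = 70 events.

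- Odds ratio = (70 × 413)/(130 × 87) = 2.56.
- Standard error of the log odds ratio = √(1/70 + 1/130 + 1/87 + 1/413) = 0.189.
- 95% CI = exp(0.9385 ± 1.96 × 0.1895) = 1.76 to 3.71.
- Fisher p = 1.1e-6, in the direction of more toxicity.

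With true rates of 35% and 17.4%, the chance of a significant result in that direction is 99.8% for 200 v 500, and 88.8% for 70 v 500.

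The plan does not say that the 500 would be genotyped afterwards. If they were, about 0.04 × 500 = 20 would be carriers. Power for 200 v 20 would be 54% at a 60% control rate and about 5% at 39%.

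**4. Group 4 as the control.** The documents give no rate or size, so both are assumed: 100 to 200 patients.

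| Assumed European rate | Chance of a significant result, study carriers at 35% |
|---|---|
| 30% | 12–16%, showing more toxicity |
| 35% | about 4%, either direction |
| 40% | 11–15%, showing less toxicity |

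**5. Group 3 as the control.** The feasibility rule requires the Clopper-Pearson 95% interval for implemented adjustments to lie wholly above 80%. Taking 200 carriers as the denominator, 171 adjusted gives a lower limit of 79.8% and 172 gives 80.4%. Meeting the rule therefore leaves at most 200 − 172 = 28 unadjusted carriers. Exact power for 172 v 28 is 67% at 35% v 60%, and about 5% if the control rate is 39%.

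**The case against.** The strongest reply is that the intended contrast is clear. The abstract names historical ungenotyped carriers, the Historical comparators section cites 39–61% for carriers without adjustment, and the hypothesis takes 60% from within that range. The article is also condensed, and the dataset may be named in a full protocol or analysis plan that is not shown. The first part stands: a matching control was evidently meant. But the article does more than omit a detail. It points the comparison to a table, repeats that list under its own heading, and leaves the matching group out of both.

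A second reply is that the protocol uses the word historical loosely, since its Historical comparators heading covers all four groups. On that reading, group 3, the unadjusted carriers in this study, could be the control. This is fair, and group 3 is indeed the right kind of patient. It cannot carry the test, however. These carriers belong to the DPYD Set being tested, they go unadjusted by choice and not by assignment, and they fall well short of 70 if the feasibility criterion is met.

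A reader might also infer that a successful trial is bound to show significant harm against its control. The documents do not support that. The reversal follows only if the 500-case review is the control, which no section says. It also rests on applying 17.4% to that review: the article gives this rate for an ungenotyped population, with two citations that also support the carrier range, and never reports 87 of 500. Nor does the article call the Fisher test primary; that it serves primary endpoint (b) is read from Table 2.

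**Conclusion.** The point holds as an inconsistency about the comparator. The hypothesis and the 70 per arm require full-dose carriers at 60%. The test names no dataset, and neither truly historical group in the table it leads to is of that kind.

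The consequence depends on the choice made: an odds ratio of 2.56 in the wrong direction against the 500-case review (assuming 17.4% and 200 carriers), roughly no difference against the European carriers (assuming a similar rate), or about 67% power against the in-study unadjusted carriers (at most 28, control rate 60%). None of the three delivers the test that was powered. The sample size arithmetic is not at fault, and the study can answer its question once a matching control is named.

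**What to change.** In Historical comparators, Table 4 and Statistical analyses, name one comparator for the Fisher test and the logistic regression: carriers of the four variants who received unadjusted fluoropyrimidine, from an identified external dataset, with its size and toxicity rate. Align this with the abstract. State that the 500-case review, the European dose-reduced carriers and the in-study unadjusted carriers are descriptive or supportive comparisons only.

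The change is to wording and needs no new data from participants, provided a suitable external dataset can be obtained. The power statement must be restated if that dataset has fewer than 70 carriers or a rate below 60%. Size alone need not be fatal: 200 v 40 still has 81% exact power at 35% v 60%. The rate matters more: at 39%, the bottom of the cited range, power for 200 v 40 is about 6%.
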